#### Demographic Data

At the initial appointment, ethnicity, maternal education, maternal work status, household deprivation (New Zealand deprivation index 18 [55]), household food security [56], and childcare use will be collected by questionnaires, using the New Zealand census questions where relevant. These data will be used to describe the sample and minimize bias.

#### Measuring Baby Food Pouch Use

This is related to primary objective 1 and secondary objectives 1, 2, 3, 5, 6, 7, and 8. We will measure the frequency of pouch use in the past month by a questionnaire. We intend to define infants as being frequent baby food pouch users if their parents state that they are currently being given food from a food pouch “5 to 6 times a week,” “once a day,” or “more than once a day,” although this may need to be modified when the distribution of intakes is determined (there are currently no published data on the frequency of baby food pouch use to base this cutoff on). We will collect data on the frequency of pouch use, use of “ready-to-eat” pouches versus “home-filled” pouches, extent to which the infant feeds directly from the pouch rather than being fed by spoon, types of foods given in “pouches,” contribution of pouch foods to total intake of solid foods, proportion of the “pouch” consumed on a typical eating occasion, duration of a typical eating occasion, physical situations in which pouches are used, proximity of an adult when the pouch is being used, reasons for using pouches rather than other methods of food delivery, and anything not liked about using baby food pouches. Key pouch questions will be asked referring to when the infant first started eating solids, when the infant was around 6 months of age, and “now.”

#### Measuring BLW

This is related to primary objective 1 and secondary objectives 1, 2, 4, 5, 6, 7, and 8. Parents will be asked to describe the way their infants were fed when they first started eating solids, when they were around 6 months of age, and “now,” using five answer options. Parents who choose “spoon fed by an adult” or “mostly spoon fed by an adult, some baby feeding themselves” will be classified as TSF. Parents who select “about half spoon feeding by an adult and half baby feeding themselves” will be classified as partial BLW [31]. Those who report “mostly baby feeding themselves, some adult spoon feeding” or “baby feeding themselves” will be assigned to full BLW [57,58]. As there is no validated definition of BLW, these definitions have been designed to capture the major point of difference between BLW and TSF, while allowing occasional adult spoon feeding.

#### Iron Status

This is related to primary objective 1. A nonfasting venipuncture blood sample will be collected at the third main appointment (3-mL EDTA anticoagulated vacutainer blood collection tube; Becton Dickinson and Company) to determine the plasma ferritin concentration and iron status defined using the body iron concentration (calculated using plasma ferritin and soluble transferrin receptor concentrations [36]) and hemoglobin concentration (from a complete blood count). The iron status categories are defined in Table 1 [54].

**Table 1 table1:** Iron status categories.

Category	Body iron value	Hemoglobin value	Plasma ferritin value
Iron sufficient	≥0 mg/kg	≥105 g/L	≥15 μg/L
Iron depleted	≥0 mg/kg	≥105 g/L	<15 μg/L
Early functional iron deficiency	<0 mg/kg	≥105 g/L	N/A^a^
Iron deficiency anemia	<0 mg/kg	<105 g/L	N/A

^a^N/A: not applicable.

As ferritin is an acute phase reactant and can be artificially elevated by inflammation, we will also analyze two inflammatory markers (C-reactive protein and α-1-acid glycoprotein) as recommended by the World Health Organization (WHO) [59]. This will enable us to use the BRINDA (Biomarkers Reflecting Inflammation and Nutritional Determinants of Anemia) statistical method to adjust for inflammation on a continuous scale, consistent with the assumption that higher concentrations of inflammatory markers will be associated with a greater effect on plasma ferritin concentration [60].

Participants will be given verbal instructions on how to apply a local anesthetic (Ametop gel; Perstorp Pharma) and will be given access to an instruction video. The gel is to be applied to the insides of both of the infant’s elbows (this enables phlebotomy to be attempted on the second arm if necessary) and covered with an occlusive dressing at least 1 hour (no more than 4-6 hours) before the blood test appointment. It is removed after 30 to 45 minutes. The blood sample will be taken by a pediatric phlebotomist. The research team has extensive experience overseeing research projects involving the collection of venipuncture blood samples from infants and toddlers [54,60,61], with 70% [54] to 92% [61] of participants providing samples.

Commercial laboratories (Southern Community Laboratories, Dunedin, New Zealand and Labtests NZ, Auckland, New Zealand) will determine complete blood count (requires fresh blood) and plasma ferritin, so that the iron status can be immediately communicated to the infant’s general practitioner if the infant is identified as having anemia. The remaining plasma will be frozen at −80°C for batch analysis of soluble transferrin receptor, C-reactive protein, and α-1-acid glycoprotein concentrations at the University of Otago Department of Human Nutrition Laboratory at the end of the study [54].

#### Anthropometry

This is related to primary objective 1. Infant weight will be measured at the initial appointment on an electronic scale (model 354; Seca) and length will be measured on a 99-cm measuring mat (model SE210; Seca) in duplicate following WHO protocols [62]. BMI (weight in kg divided by height in meters squared) will be calculated, and BMI-for-age z-scores will be determined using WHO reference data [63]. We will also request consent from parents to collect information on BMI from the B4 School Check [64] when the children are 4 years of age. This will enable us to look at the effects of pouches and BLW on growth longitudinally.

#### Infant Diet

This is related to secondary objective 1. Information on infant nutrient intake and adequacy, food group intake, dietary patterns, and culturally important foods will be obtained using interviewer-administered multiple pass 24-hour recalls collected at the first and second appointments. The two 24-hour recalls take place on different days of the week to capture variation in intake between days. Collecting two 24-hour recalls will enable us to calculate “usual intake” using the multiple source method (MSM) for estimating usual dietary intake of individuals [65]. Photograph prompts will be used to assist recall of foods eaten. Participants will be asked to photograph (using their own smartphone or a camera provided) the eating surface (eg, plate, high chair surface, and table) at the start of all meals and snacks from midnight to midnight on the day before the appointment. The quality of the photographs will not be important as long as they are clear enough to remind the parent what the child ate. Diet recalls will be analyzed with FoodWorks (version 10, Xyris Software) using the New Zealand Food Composition database FOODfiles 2018 Version 01 [66]. Nutrient information for commercial infant foods and milk will be determined by generating recipes using the ingredients lists on food products modified to match the nutrient information panel on the packet so that the contribution of nutrients that do not appear on the nutrient information panel can be included [15]. Information on supplement use will be collected by a questionnaire.

Particular focus will be on free sugars and added sugars given a recent small study [45] suggested that even by 7 months of age, 12% of New Zealand infants may already be consuming free sugars at levels that are above the WHO recommendation [67]. Parents are discouraged from adding sugar to infants’ diets because it is unnecessary and may increase liking of sweet foods [2]. In addition, the WHO recommends that free sugars should be <5% of energy intake due to the dose-response relationship between free sugar intake and dental caries (even in populations with water fluoridation) [67]. Data on free sugars and added sugars are available in the New Zealand food composition database [66,68].

Questionnaire and 24-hour recall data will also be used to determine the extent to which key indicators of diet quality are being met, as guided by the New Zealand Ministry of Health Eating and Activity Guidelines for New Zealand Infants and Toddlers [2].

#### Breast Milk Intake

This is related to secondary objectives 1 and 2. We will obtain accurate data on the amount of breast milk infants consume using the stable isotope (deuterium oxide) “dose-to-mother” technique [48-50] in a consecutive sample of 150 breastfeeding mother-infant dyads. This will enable us to measure intake to ±34 mL/day (ie, 5% of expected total intake [47]) at a 95% precision level. The isotope will be administered to the mother orally at the initial appointment (after collection of the baseline saliva sample), and saliva samples will be collected from the mother and infant at three further appointments to measure the disappearance of the deuterium from the mother and appearance in the infant. Baseline and three postdose sampling points (days 2-3, 7-9, and 13-14) are required to achieve adequate accuracy and precision of human milk intake. Height/length and weight will be measured at baseline, with weight measured again at the final appointment for both mother and infant, so that breast milk intake can be calculated. Breast milk intake data will be used along with questionnaire and recall data to generate predictive equations of breast milk intake so that intake can be estimated for participants who did not have breast milk intake measured.

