Although the foods offered in baby food pouches are broadly similar in content to those offered as baby foods in jars and cans, there has been some concern, albeit not universal [15], that the content of added sugar might be higher [10,13,14,16]. Certainly, cereal products in pouches are a poor source of iron and should not be used to replace iron-fortified infant cereals [15]. Regardless of nutrient content, the delivery method itself has the potential to markedly change infant nutrition for several reasons. Anecdotal reports suggest food products are being consumed straight from the pouch, unsupervised, and “on the go,” so they are outside usual eating contexts. This could have a number of important impacts on infant health and development.

First, these smooth highly processed products with multiple blended ingredients bear little resemblance to intact fruits and vegetables, and they are marketed well beyond the early weeks of complementary feeding when it might be argued a “super smooth” product is appropriate (eg, many are marketed for infants 8 months plus). This raises a number of questions. Do these products increase energy intake because they are so easy to eat (smooth consistency and do not require chewing; an entire 120-g serve can be accessed merely by squeezing the soft pouch and sucking)? Conversely, does the ease of consumption lead to displacement of other more nutrient-rich foods, such as breast milk (or infant formula), from the diet (eating “on the go” is unlikely to be consistent with New Zealand Ministry of Health recommendations that until 8 months of age infants are offered solid foods after milk to avoid displacing nutrient-rich milk [2])? Certainly, the structure of baby food pouches is described as “facilitating rapid passage of solid foods” [12], which suggests overeating is possible.

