
Infant milk (breastmilk or infant formula) is a substantial component of the diet for infants during the complementary feeding period, providing more than half of their energy intake at 7 months of age [44]. While it is straightforward to estimate intake of infant formula for those who consume it, researchers currently have to use a “one size fits all” approach to estimate breast milk intake, either using a single volume for all breastfed infants of a particular age [45] or excluding breastfed infants from dietary analyses [46]. Neither approach is ideal because breast milk intake varies considerably between mother-infant pairs [47] and because breastfed infants do not necessarily have the same food intake or socioeconomic background as formula fed infants. The conventional method used to measure breast milk intake is to weigh the infant before and after every feed. However, this “test-weighing” technique is time consuming and may disturb usual feeding patterns. In contrast, the stable isotope deuterium oxide technique requires the mother to consume a small amount of the stable isotope (deuterium oxide) in water, and the amount of this marker transferred to the infant (ie, via the breast milk the infant consumes) is then measured by collecting saliva samples from the mother and infant over the following fortnight [48-50]. The normal feeding pattern is not disturbed, and the total volume of breast milk consumed by the infant over the fortnight can be accurately assessed. The use of this technique will allow the First Foods New Zealand (FFNZ) study to collect data that will enable more accurate estimates of nutrient intake in this age group and allow us to generate predictive models that use infant and diet characteristics that are routinely measured to estimate breast milk volumes. Such models would be invaluable for estimating total nutrient intake for breastfeeding infants (69% of infants at 4-8 months in New Zealand [51]) in future studies.

The FFNZ study will determine the iron status, growth, food and nutrient intakes, breast milk intake, eating and feeding behaviors, dental health, oral motor skills, and choking risk of New Zealand infants, with a particular focus on the use of baby food pouches and BLW.

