### Secondary Objectives

In infants aged 7.0 to 9.9 months, we will estimate the following: (1) Nutrient intake, nutrient adequacy, and foods of cultural importance in New Zealand infants and in infants fed using baby food pouches regularly or those following BLW; (2) Breast milk intake in New Zealand infants and in infants fed using baby food pouches regularly or those following BLW; (3) Prevalence and nature of food pouch use; (4) Prevalence of BLW; (5) How eating behaviors (ability to eat with appetite, speed of eating, and picky eating) and feeding behaviors (parental responsiveness to infant hunger and satiety cues) differ according to the extent of food pouch use and complementary feeding approach (BLW compared with TSF); (6) How dental health differs according to the extent of food pouch use and complementary feeding approach (BLW compared with TSF); (7) How oral motor skills differ according to the extent of food pouch use and complementary feeding approach (BLW compared with TSF); and (8) How the risk of choking differs according to the extent of food pouch use and complementary feeding approach (BLW compared with TSF).

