### Data Collection

#### Overview

Participation in the study will involve three (participants in the main study) or five (participants in a consecutive subsample of breastfed infants) contacts over 2 weeks following recruitment. For the main study (n=625), the first main appointment will generally be held in the participant’s home and involve a 24-hour diet recall, completion of two questionnaires, and anthropometric measurements of the child. The second main appointment will generally take place at university research rooms, and involve a second 24-hour diet recall and photography of the infant’s teeth to assess dental health. A third main appointment will take place at our university rooms (Dunedin) or a local blood testing facility (Auckland) to collect a blood sample to measure the iron status. Finally, a self-administered questionnaire will be completed by the participants in their homes. For the subsample (n=150) involved in the measurement of breast milk intake, a stable isotope will be given at the first main appointment, with three additional saliva samples collected over the ensuing fortnight (the third sample being collected at the second main appointment).

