Nutrient intake will be determined using 24-hour recall data adjusted to provide estimates of usual intake (using the MSM method [65]). Adequacy of intake will be determined as follows: for zinc (for which an estimated average requirement [EAR] is available for New Zealand and Australia [82]), the EAR cut point method will be used; for iron (for which an EAR and tables of probabilities of inadequate intakes are available for the United States of America and Canada [83]), the full probability approach will be used [83]; for other nutrients (only an adequate intake [AI] is available for this age group in New Zealand and Australia [82]), mean group intake above the AI will be considered to indicate adequacy, but a conclusion as to inadequacy will not be possible if mean group intake is below the AI [84]. The BRINDA method [60] will be used to adjust plasma ferritin, and therefore, body iron and iron status, for the impact of inflammation.

The best-fitting polynomials to predict breast milk intake will be estimated by regression models using fractional polynomial functions of variables, such as age, sex, body weight, and food and beverage intake (eg, kJ/day). This will result in equations that can be used to predict breast milk intake based on a variety of input variables. Ideally one based on data that can be collected in a single clinical appointment, and another that uses data requiring more extensive collection in a research or surveillance setting.

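### Breast milk intake for unmeasured breastfed infants is to be filled in with single regression predictions, which, used as they stand, lose between-infant spread and give confidence intervals that are too narrow

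*Protocol article*

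**What the plan says.** Under Breast Milk Intake, the protocol article measures intake "in a consecutive sample of 150 breastfeeding mother-infant dyads" and expects to "measure intake to ±34 mL/day (ie, 5% of expected total intake [47]) at a 95% precision level". These measurements, together with the recalls and questionnaires, have a second stated use: "generate predictive equations of breast milk intake so that intake can be estimated for participants who did not have breast milk intake measured". The section states that it serves secondary objectives 1 and 2.

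Statistical Analysis gives the method: "The best-fitting polynomials to predict breast milk intake will be estimated by regression models using fractional polynomial functions of variables". Age, sex, body weight and food and beverage intake are given as examples. The same paragraph wants one equation for a single clinical appointment and another for research or surveillance.

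Secondary objective 2 is "Breast milk intake in New Zealand infants and in infants fed using baby food pouches regularly or those following BLW". Objective 1 covers nutrient intake and adequacy in the same groups. Statistical Analysis plans comparisons of energy and nutrient intake between pouch users and nonusers, 95% CIs for intake and adequacy, the EAR cut point method for zinc and the full probability approach for iron. The Background asks of pouches: "does the ease of consumption lead to displacement of other more nutrient-rich foods, such as breast milk".

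**The concern.** A best-fitting equation returns a conditional mean. Entered as an infant's milk intake, it is a single imputation without residual variation. Three consequences follow.

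- **Spread.** Predicted intakes vary less between infants than true intakes. The zinc and iron adequacy methods depend on the distribution of total intake, and the Background says that milk gives more than half of energy at 7 months. It also faults a single volume for all breastfed infants because intake varies considerably between pairs; predictions only partly cure that.
- **Precision.** A standard error computed as if every value had been measured ignores both the residual variance and the uncertainty of an equation fitted to 150 infants.
- **Group differences.** If the equation leaves out pouch use and BLW, any part of a true difference that the other predictors do not carry is absent from the predicted infants.

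At stake are the milk and total nutrient results of secondary objectives 1 and 2. The primary outcomes, iron status and BMI z-score, are untouched.

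**Working it through.** **Inputs from the article.** Sample 625 (Overview); 150 measured dyads and ±34 mL/day, being 5% of expected intake (Breast Milk Intake); 69% breastfed at 4-8 months (Background); 29% BLW (Sample Size). **Assumptions.** R² of the equation 0.2-0.6; 50-65% breastfed as an alternative rate; in the simulation, a true group difference of 68 mL/day.

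**1. The plan's own figure.** Expected mean = 34/0.05 = 680 mL/day. No SD is given, so ±34 can only be solved backwards: SD = 34 × √150 / 1.96 = 212 mL/day, or 31% of the mean. The figure is coherent but cannot be reproduced independently.

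**2. Number predicted.** 0.69 × 625 = 431 breastfed; 431 − 150 = 281, or 65% of them. The 69% is for 4-8 months and the study enrols at 7.0-9.9 months, so 281 is probably an upper figure. At 50%: 312.5 − 150 = about 163 (52%). At 65%: 406 − 150 = 256 (63%).

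**3. Spread.** SD of predictions = 212 × √R². With w = 281/431 = 0.652, the SD of measured and predicted infants together, relative to the true SD, is √[(1 − w) + w·R²].

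| R² | SD of predictions (mL/day) | Share of true SD, predicted only | Share of true SD, all 431 |
|---|---|---|---|
| 0.2 | 95 | 45% | 69% |
| 0.4 | 134 | 63% | 78% |
| 0.6 | 165 | 77% | 86% |

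**4. Precision of the overall mean.** The naive SE, with predictions treated as data, is 212 × √[((1 − w) + w·R²)/431]. The actual SE is about 212 × √[(1 − R²)/150 + R²/431].

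- R² = 0.2: naive 7.1, actual 16.2; 95% half-widths ±14 and ±32 mL/day.
- R² = 0.6: naive 8.8, actual 13.5; half-widths ±17 and ±27 mL/day.

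The ±34 mL/day from the 150 measured infants alone would therefore appear to halve or better, while the real gain is small to moderate.

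**5. Group difference.** Simulation with 4,000 replicates, 431 infants, 150 measured, 29% BLW, and measured and predicted infants pooled. Ranges are over R² of 0.2, 0.4 and 0.6.

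| Analysis | Difference retained | Coverage of nominal 95% CI |
|---|---|---|
| Group not in equation, predictors carry none of it | 34-35% | 20-38% |
| Group not in equation, predictors carry half | 68-69% | 70-79% |
| Group not in equation, predictors carry all | 100% | 90-94% |
| Group in equation, predictions treated as data | about 100% | 60-81% |
| 150 measured infants only | 100% | 94-95% |

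In the first two rows coverage fails mainly through bias. With group in the equation it fails through the standard error: naive 15.6-19.4 against actual 30-37 mL/day. The measured infants alone give 38-39 mL/day, so adding predictions gains little real precision for this contrast.

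**The case against.** The strongest objection is that the article does not fix the analysis being criticised. The predictor list is illustrative. Questionnaire data are named as an input to the equations, and pouch use and BLW are questionnaire items, so feeding group may well be included. A reader might infer that the plan excludes them and will lose about two thirds of any milk difference. The documents do not support that: the omission is not stated, and a loss of that size needs the other predictors to carry none of the difference. Food energy, a plausible route for displacement, is itself a named example. No passage says that group contrasts in milk will pool measured and predicted infants, and the only stated precision belongs to the 150. This part of the objection stands, and the shrinkage is conditional.

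It is also fair that residual draws and error propagation may sit in an analysis plan that is not shown. This stands only in part. The article does not merely omit a detail; it names best-fitting regression as the means of supplying intake for unmeasured infants and ties the section to objectives 1 and 2. Followed as written, that is single conditional-mean imputation, and its intervals are too narrow even when feeding group is in the equation.

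Finally, a reader might infer that the zinc and iron adequacy results will be materially wrong. The article gives neither the zinc nor the iron content of milk, so the direction of the effect on spread is clear but its size in total nutrient intake is unknown.

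**Conclusion.** The concern holds for spread and precision, and conditionally for group differences. Predictions used as they stand would have an SD of 95-165 mL/day against an implied 212, and confidence intervals for milk intake, and for nutrient totals built on it, would be too narrow. For the overall mean the apparent half-width would be ±14 to ±17 mL/day against a true ±32 to ±27. Pouch and BLW differences shrink only if feeding group is left out of the equation and the remaining predictors do not carry the whole effect; 34% to 100% of the difference is then retained.

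These sizes rest on an assumed R² of 0.2-0.6, on an SD solved backwards from the stated precision and, for the standard errors and the simulation, on the 69% breastfeeding rate. With a lower rate fewer infants are predicted, but still more than half of those breastfed at the rates tried. Only secondary objectives 1 and 2 are affected. The matter should be changed before analysis; it does not threaten the primary objective.

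**What to change.** For the study's own analyses of objectives 1 and 2, treat unmeasured milk intake as planned missing data. Replace single predicted values with multiple imputation that draws both residuals and model parameters, has pouch frequency and BLW group in the imputation model alongside the existing predictors, and is combined by Rubin's rules. Carry the imputed values through to the usual-intake and adequacy estimates.

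Name the 150 measured infants as the primary basis for pouch and BLW contrasts in breast milk intake, with the imputed whole-sample contrast as supporting. Keep the prediction equations for clinic and surveillance use as a separate product, since they serve a different purpose from the group comparisons.

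The cost is extra analysis work and somewhat wider confidence intervals. No new data are needed.
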